### 3.1. Primary outcomes

The primary outcome will be the severity of depression symptoms evaluated by the MADRS (Montgomery and Asberg, 1979), an item with 10 parts to evaluate depressive symptoms. It is one of the most extensively used tools for assessing the degree of PPD in clinical practice (Fernandes et al., 2019). Every item of the MADRS is scored on a seven-point scale (from 0 to 6). The higher the score, the more severe the depression, with a total score of 0–60. A total score of ≥35 indicates extreme depression, 30–34 indicates major depression, 22–29 indicates moderate depression, and 12–21 indicates mild depression (Hudgens et al., 2021).

### 3.2. Secondary outcomes

The Perceived Stress Scale (PSS) (Cohen et al., 1983) is a commonly used self-report tool for evaluating the extent to which situations in an individual's life are rated as stressful. The items involved in this scale are devised to assess the extent to which respondents found their lives unpredictable, uncontrollable, and overloaded in the past month. The PSS includes 14 items on a five-point scale ranging from 0 (never) to 4 (very often), with a total score of 0–56. Higher scores indicate increased levels of perceived stress. The European Spanish version of the PSS will be used in the study (Remor, 2006).

The Positive and Negative Affect Scale (PANAS), which provides an assessment of these affects, will be used in this study (Watson et al., 1988). Participants will be asked to rate the degree of each emotional state they experienced on a Likert-type scale ranging from 1 (very mild or not at all) to 5 (exceedingly or very severe), resulting in a total score ranging from 10 to 50.

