## 2. Method

### 2.1. Study design

The RCT will involve recruiting patients with PPD for up to 1–2 years from professional postpartum psychological health projects in the Departments of Psychosomatic Medicine, Rehabilitation Medicine, Obstetrics, and Gynecology at the First Affiliated Hospital of Nanchang University. To recruit enough participants, leaflets and posters will be posted at the place of recruitment, and physicians will be informed about this study to assist in identifying qualified participants. The research coordinator conducted a baseline visit before the start of the active study to collect information on baseline demographics, to gain access to health services, and to gather baseline Montgomery-Asberg Depression Rating Scale (MADRS) measures.

In addition to the intervention, sham control will also be carried out within the Core Clinical Experiment at the first Affiliated Hospital of Nanchang University by well-trained researchers to guarantee proper supervision throughout the procedures. The active period of the experiment involving altogether 18 intervention or sham control sessions lasting for 20 min for approximately 3 weeks (6 days per week). The researchers who manage the session will record the date of every visit, the participant's blood pressure and heart rate, the starting and finishing times of sham tDCS, and interruptions, if any. All confounding factors (such as a previous history of depression, treatments, family history, etc.) will be analyzed. Outcome questionnaires will be collected from patients with PPD at three time points: before the procedures after enrollment (T1), 1 week after completing the procedures (T2), and 3 weeks after completing the procedures (T3). Follow-up questionnaires will be completed in person or by phone 8 weeks after completing the procedures. Patients will receive email updates concerning enrollment goals and the integrity of follow-up to help them to perceive the contributions that they made while participating in the study. Participants are then contacted with outcome information gathered and organized by professionally trained and experienced researchers. Personal outcome information is blind to the researchers, participants, and physicians who provided clinical treatment and care in the study group assignment.

The flow diagram of this study design is shown in Figure 1, and the evaluation of different time points is shown in Table 1.

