### 2.3. Eligibility criteria

To be included in the study, the participants must meet the following criteria:

(1) Be postpartum and at least 18 years old;

(2) Satisfy the current criteria for the diagnosis of severe depression or at least a severe depression paroxysm of moderate severity based on the fifth edition of the Diagnostic and Statistical Manual of Mental Disorders (DSM-5);

(3) Have been provided with and have refused to take antidepressants prescribed by their attending clinicians at the recruitment location;

(4) Be evaluated to qualify for outpatient psychiatric treatment by a chief researcher; and

(5) Have never received tDCS but agree to this treatment approach and comprehend the interpretations of the study and the associated questionnaires.

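### The protocol fixes a European Spanish form of the self-report PSS for women recruited only in Nanchang; PSS timing and the PANAS score also need clarifying

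*Protocol article*

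**What the plan says.** All references are to the protocol article.

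**Language.** Section 3.2 says "The European Spanish version of the PSS will be used in the study". It also says that the PSS "is a commonly used self-report tool for evaluating the extent to which situations in an individual's life are rated as stressful". Section 2.1 places recruitment in the departments of psychosomatic medicine, rehabilitation medicine, "Obstetrics, and Gynecology at the First Affiliated Hospital of Nanchang University", and section 2.2 screens at the same hospital. Criterion 5 of section 2.3 requires that participants "comprehend the interpretations of the study and the associated questionnaires". Spanish-speaking participants, a Chinese form and a translation step are mentioned nowhere.

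**Recall and timing.** Section 3.2 says the items ask how far respondents "found their lives unpredictable, uncontrollable, and overloaded in the past month". Three places describe when questionnaires are given:
- The abstract has the PSS and PANAS before and after the intervention.
- Section 2.1 has outcome questionnaires at baseline (T1), 1 week after the procedures (T2) and 3 weeks after them (T3), with a follow-up questionnaire at 8 weeks.
- Table 1 has both scales at screening, in each of treatment weeks 1, 2 and 3, and at the 8-week follow-up.

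**PANAS.** Section 3.2 refers to positive and negative affect, has items rated from 1 to 5, and describes the score as "resulting in a total score ranging from 10 to 50". It gives no number of items, no separate scores and no direction.

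**The concern.** The language statement is a positive specification, not a detail left to a fuller document. A woman who does not read Spanish cannot give a meaningful answer to a Spanish self-report form, and responses on an unsuitable form cannot be repaired in analysis. The PSS is one of only two scales named as secondary outcomes.

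The other two points are smaller. A scale that looks back a month, given during a 3-week treatment, partly measures the time before treatment. Those days carry no treatment effect in either arm, so they are expected to pull the difference between arms towards zero. For PANAS, a reader cannot tell which score will be compared, or in which direction a change is favourable.

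**Working it through.** **1. Language.** Three statements are set side by side: a European Spanish self-report form (3.2), recruitment only in Nanchang (2.1, 2.2), and a requirement to understand the questionnaires (2.3). If the participants are Chinese speakers, which the article does not say and is assumed here, the three cannot all be carried out. The inconsistency is one of wording, and no arithmetic applies.

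**2. PSS range.** The article says: "The PSS includes 14 items on a five-point scale ranging from 0 (never) to 4 (very often), with a total score of 0–56". Check: 14 × 0 = 0 and 14 × 4 = 56. The stated range reproduces, so the scoring is sound. The language form and the timing are what need attention.

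**3. Recall window.** Inputs: a past-month recall (3.2) and 3 weeks of treatment, or 21 days (2.11). The length of the month, *m*, is not given and is taken as 28 or 30 days. With *d* the number of days since treatment began, the share of the window before treatment is max(0, *m* − *d*) / *m*.

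| Time point | Source | *d* | *m* = 30 | *m* = 28 |
|---|---|---|---|---|
| End of week 1 | Table 1 | 7 | 23/30 = 77% | 21/28 = 75% |
| End of week 2 | Table 1 | 14 | 16/30 = 53% | 14/28 = 50% |
| End of week 3 | Table 1 | 21 | 9/30 = 30% | 7/28 = 25% |
| T2, 1 week after | 2.1 | 21 + 7 = 28 | 2/30 = 7% | 0% |
| T3, 3 weeks after | 2.1 | 21 + 21 = 42 | 0% | 0% |
| 8-week follow-up | 2.1, Table 1 | 21 + 56 = 77 | 0% | 0% |

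The overlap is large only at the on-treatment visits in Table 1. The later time points lose something else. At T3, 70% of a 30-day window (75% of 28 days) lies after treatment has ended, and at the 8-week visit all of it does.

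**4. PANAS range.** With items scored 1 to 5, a minimum of 10 implies 10/1 = 10 items and a maximum of 50 implies 50/5 = 10 items. The stated range therefore fits exactly 10 items: either one total over 10 items, or the range of each of two 10-item scores. A sum over 20 items would run from 20 to 100.

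**The case against.** **The language sentence may be a slip in the article.** The wrong version may have been named or cited while a Chinese form is used in practice, and criterion 5 names no language. This is plausible, but the remedy is the same, because the article must say which form is used. It does weaken one inference a reader might draw, that criterion 5 would exclude nearly every candidate. That depends on the assumed language of the participants and on the Spanish form really being handed out. The figure of 240 is a worst case for the same reason.

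**The recall point depends on the schedule.** This stands. The 77%, 53% and 30% apply only if Table 1 governs. A reader of Table 1 might infer that the 8-week visit is the only one free of pre-treatment time. Section 2.1 does not support that, since T2 has at most 7% overlap and T3 has none. Overlap dilutes a difference but does not make the score meaningless. At the end of week 3, 70% of a 30-day window is on treatment. Making week 8 the main comparison would exclude the treatment period altogether, so it is a trade-off and not an obvious correction.

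**PANAS may already be two scores.** This also stands. A reader might infer that positive and negative items are added together, so that a rise in one affect cancels a fall in the other. The article does not say so, and the range of 10 to 50 is compatible with separate scores.

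**The broad conclusion that the secondary outcomes would not measure what is intended** goes too far. It is supported for the PSS language form, but not for PSS recall or PANAS.

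**Conclusion.** The language specification is wrong as written and should be corrected before the PSS is used. This rests on the assumption that women recruited in Nanchang are Chinese speakers; nothing in the article points the other way. It affects one secondary scale, for up to all 240 planned participants if the sentence is followed literally.

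The recall point is conditional. On Table 1's schedule, and with a month of 28 to 30 days, 75–77%, 50–53% and 25–30% of the window precedes treatment at weeks 1, 2 and 3. On section 2.1's schedule the overlap is 0–7% at T2 and nil at T3. What is certain is that the three descriptions of timing disagree.

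The PANAS point is an unclear score definition and no more. The primary MADRS outcome and the sample size are not touched by any of this.

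**What to change.** 1. In section 3.2, replace the sentence on the European Spanish version with the Chinese-language version of the 14-item PSS to be used, and cite its validation source. If the Spanish version is intended, justify it. The article does not show which validated Chinese form is available, so the investigators must supply this. If any PSS data have already been collected, state which form was used.
2. Reconcile the abstract, section 2.1 and Table 1 on when the PSS and PANAS are given. Set the main PSS comparison at one stated time point whose recall window holds little or no pre-treatment time, for example T2 or T3 of section 2.1. Earlier PSS scores, if kept, can be described with the overlap acknowledged.
3. State that PANAS positive and negative affect are scored separately, each from 10 to 50, and give the direction that counts as improvement for each.

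The cost is protocol wording and, if the Spanish form is really in use, a different form. The one real trade-off is in item 2: a later PSS time point avoids pre-treatment days, but the answer comes after the end of treatment and, the later it is set, reflects persistence more than the on-treatment effect.

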### 3.3. Follow up

After the three-week treatment, an eight-week follow-up will be performed. The participants will be contacted by medical staff by phone or in person. Additionally, participants will be contacted every 2 weeks to document their medication and recovery. During the final week of the follow-up process (week 8 of post-intervention), the participants can be referred for a clinical evaluation to evaluate their prognosis and their status of disability.

### 3.4. Statistical methods

The results of the test will be analyzed using the Statistical Package for the Social Sciences, version 21.0. In the descriptive analysis of the samples, continuous variables with normally distributed data will be expressed as means and standard deviations whereas continuous variables with non-normally distributed data will be expressed as medians and interquartile ranges. Statistical comparisons of normally distributed data packages between *t*-test groups will also be performed. Ordinary-level variables with non-normal distributions will be compared statistically using the Mann–Whitney *U* test. Metrics with discrete distributions will be expressed as percentages and analyzed using χ^2^ or Fisher's exact test, as applicable. The general linear or logistic models will be used if needed to adjust the obfuscation effect.

To compare the baseline characteristics between the intervention group and the control group, the *t*-test or Mann–Whitney *U*-test will be used. If statistically significant, the inequalities will be considered for confounding factors in the final efficacy analysis. To compare one or two outcomes between the two groups, continuous data will be analyzed using the *t*-test or the non-parametric test, and the data will be parsed using the Pearson χ^2^ test or Fisher's precision test. To control for possible confounding variables, linear models or linear regression models will be used for dependent continuous and dependent categorical variables. Repeating measure data will be used in the analysis of variance. The primary and secondary outcomes analyses will depend on intention-to-treat (ITT) and per-protocol (PP) bases. The results from ITT analyses will be compared with those from PP analyses to determine whether they are consistent. Missing data will be used as the final bearer for observation. The side effects will be displayed and parsed using a χ^2^ test or Fisher's precision test.

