### 2.5. Sample size

The sample size involved in this study will be based on that of previous studies. The improvements will be evaluated using identical sample sizes based on the following estimated formula:

$\eta =\frac{2\bar{pq}{\left(Z_{\alpha }+Z_{\beta }\right)}^{2}}{{\left(p_{1}-p_{2}\right)}^{2}}$. The first type of error is 5% (α = 0.05) and 90% power (β = 0.10), and the estimated sample size requires 79 participants per group. Given the high drop-out rate (~15–20%) in the study (Lever Taylor et al., 2016), at least 198 participants will be required to achieve the target of 79 participants in each group. We receive approximately 200 patients with PPD per month, combined with approximately 120 patients suffering from moderate to major depressive disorders. According to the recruitment approach of a previous study (Walton et al., 2014), we estimate that 60 patients (50%) may be ineligible owing to antidepressant-based treatment 15 patients may be ineligible for various reasons such as having severe physical diseases or complications, and 20 patients within the remaining 45 patients (50%) may agree to participate in the preliminary study. Therefore, the enlisting of 240 patients suffering from PPD could be achieved within a year.

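### The only stated missing-data rule reads as last observation carried forward, which shrinks a true MADRS effect and can create a false one if drop-out differs between arms

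*Protocol article*

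**What the plan says.** Section 3.4 (Statistical methods) states one rule for missing outcomes: "Missing data will be used as the final bearer for observation". It directly follows the analysis sets: "The primary and secondary outcomes analyses will depend on intention-to-treat (ITT) and per-protocol (PP) bases", with the two sets of results compared for consistency. For group comparisons the section says that "continuous data will be analyzed using the *t*-test or the non-parametric test", and for the repeated visits that "Repeating measure data will be used in the analysis of variance". Linear models are allowed for adjustment. No mixed model, multiple imputation or missing-data sensitivity analysis is named.

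Other sections show how much missingness the rule may have to carry:

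- Section 2.5 (Sample size): "Given the high drop-out rate (~15–20%) in the study". No split by arm and no timing is given.
- Section 2.11.1 (Basic treatment): starting an antidepressant is recorded and ends participation.
- Section 2.12 (Study endpoints): early discontinuers stay in the intention-to-treat analysis, with follow-up obtained only if they are willing.
- Table 1: MADRS, the primary outcome in section 3.1, is taken at screening, weeks 1, 2 and 3, and the 8-week follow-up.

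**The concern.** LOCF assumes that a patient's score stops changing at the last visit attended. In depression trials, scores usually fall in both arms during treatment. A patient who leaves early is then credited with too little improvement, and the shortfall is larger the earlier she leaves.

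Two consequences follow. If both arms lose patients equally, the arm with the larger true fall loses more of it, so the treatment difference shrinks. If one arm loses more patients, or loses them earlier, that arm looks worse whatever the treatment does. Such an imbalance is plausible here, because starting an antidepressant, worsening and adverse reactions can all end participation or treatment, and any of them may depend on the arm.

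The filled values enter the intention-to-treat analysis of the primary outcome. The article presents the trial as a guide to a larger multi-centre study (sections 1 and 4), so the estimate would be carried into that design.

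**Working it through.** **The plan's own figure.** Section 2.5 says that "the estimated sample size requires 79 participants per group". Allowing for 20% loss: 79 / 0.80 = 98.75, so 99 per arm and 198 in total, as stated. At 15%: 79 / 0.85 = 92.9, so 93 per arm and 186 in total. The enrolment target of 240 is 120 per arm. Both 99 and 120 are used below.

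**Assumptions (none is in the article).** Sham MADRS falls 9 points in a straight line to week 3. The true difference is 0 or 4.5. SD is 8 at each visit. Drop-out is unrelated to score. Two timing patterns are compared:

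- Early: last score at baseline, week 1 or week 2, one third each.
- Late: last score at week 1, 2 or 3, one third each.

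**Bias.** Let F be an arm's true fall by week 3, d its drop-out fraction and g the mean share of the fall already seen at the last visit. The expected LOCF fall is F × [1 − d(1 − g)].

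- Early: g = (0 + 1/3 + 2/3)/3 = 1/3, so the fall is F(1 − 2d/3).
- Late: g = (1/3 + 2/3 + 1)/3 = 2/3, so the fall is F(1 − d/3).

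| Scenario (active v sham drop-out) | Early | Late |
|---|---|---|
| True 4.5, 17.5% v 17.5% | 4.5 × (1 − 0.117) = 3.98 | 4.5 × (1 − 0.058) = 4.24 |
| True 0, 10% v 25% | 9 × 2/3 × 0.15 = 0.90 | 9 × 1/3 × 0.15 = 0.45 |
| True 0, 15% v 20% | 9 × 2/3 × 0.05 = 0.30 | 9 × 1/3 × 0.05 = 0.15 |
| True 4.5, 25% v 10% | 13.5 × 0.833 − 9 × 0.933 = 2.85 | 13.5 × 0.917 − 9 × 0.967 = 3.68 |

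Simulation with a lag-1 correlation of 0.6 gave the same values within simulation error: 3.97, 0.90, 0.27 and 2.84 for early exits; 4.24, 0.44–0.45 and 3.65 for rows 1, 2 and 4 with late exits.

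**Type I error, 10% v 25%, no true effect.** LOCF adds a variance v = d × mean(s²) − [d × mean(s)]² to each arm, where s is the fall missed by a patient who leaves.

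- Early: s = 9, 6, 3, with mean 6 and mean square 42. Active v = 4.2 − 0.36 = 3.84; sham v = 10.5 − 2.25 = 8.25. With 99 per arm, SE = √[(64 + 64 + 3.84 + 8.25)/99] = 1.19 and 0.90/1.19 = 0.76. Type I error = Φ(−1.20) + Φ(−2.72) ≈ 0.12 (simulated 11.5–12%). With 120 per arm, SE = 1.08 and the error is about 0.13 (simulated about 14%).
- Late: s = 6, 3, 0, with mean 3 and mean square 15. Active v = 1.41; sham v = 3.19. With 99 per arm, SE = 1.16 and 0.45/1.16 = 0.39. Type I error ≈ 0.07 (simulated about 6–7.5%).

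With balanced 17.5% drop-out and no true effect the bias is zero, and simulated type I error was 0.046–0.050. At 15% v 20% with early exits it was about 6%.

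**Power.** For a true 4.5 and 25% v 10% drop-out, simulated power was about 63% (99 per arm) and 71% (120 per arm) with early exits, and 87% and 93% with late exits. With no drop-out and 99 per arm it was 98%.

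**Second set of assumptions.** Sham fall 14, week-3 SD 9, correlation 0.7, true difference 4, early exits, 99 per arm:

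- Balanced 15% and 20% drop-out gave 3.59 and 3.44, a shrinkage of 10% and 14%. Power of the week-3 t-test fell from 0.87 to 0.74 and 0.70.
- With no true effect, 10% v 20% gave 0.93 points and a type I error of 0.11 (t-test) to 0.16 (uncorrected repeated-measures ANOVA).
- With no true effect and 20% lost in each arm, but later exits in active than in sham, the result was 1.12 points and 0.14–0.18.
- With a true 4, 30% v 10% gave 1.36 and 10% v 30% gave 5.59, so the bias can run either way.

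**Check on the cause.** In the same simulations, the week-3 difference in participants with complete data was unbiased: 4.48–4.49 for a true 4.5, 3.96–4.00 for a true 4, and about 0 under no effect. The bias therefore comes from LOCF and not from the simulated drop-out.

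**The case against.** The strongest reply is that the harm is conditional and its size rests on invented inputs. Much of that stands.

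- **Error rate.** A reader might infer that LOCF with 15–20% drop-out always distorts the type I error. The article gives no arm split or timing, and with balanced drop-out and no true effect the t-test stays near 5%. A 15% v 20% split, which stays within the article's range, gives only about 6%.
- **Timing.** If patients leave after weeks 1–3, the bias is half that of the early pattern. Section 2.5 does not say what period its drop-out rate covers.
- **Standard errors.** A reader might infer that LOCF makes standard errors wrong in general. For a t-test on one carried-forward value per patient this is not so: the values are independent and their observed variance is used. The inflation comes from bias in the mean.
- **ANOVA.** The sequence of LOCF followed by repeated-measures ANOVA is an inference, since section 3.4 also names t-tests, non-parametric tests and linear models. Uncorrected ANOVA gave 0.064 with no drop-out and about 0.07 with balanced drop-out, so LOCF added little there.
- **Follow-up.** Sections 2.12 and 3.3 provide for continued contact, which should reduce missing outcomes, though only for willing participants.

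It may also be said that shrinkage under balanced drop-out is conservative. That holds only for that pattern. Since the pattern is unknown in advance, LOCF cannot be called conservative here.

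Nor can the matter be left to an unseen analysis plan: the article has chosen and stated a rule. The comparison with per-protocol results is no safeguard, because that set would ordinarily omit many of the same drop-outs.

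**Conclusion.** The concern holds in conditional form. The plan's single missing-data rule reads as LOCF, and a better method is available from visits already planned. If MADRS falls over time, LOCF shrinks a true effect by about 6–14% under balanced drop-out of 15–20%. It creates a spurious difference, in either direction, if drop-out rates or timing differ between arms. At an assumed 10% v 25% and no true effect, that is about 0.4–0.9 points and a type I error of about 6–14%, depending on timing and on 99 or 120 per arm.

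These figures rest on assumed trajectories, SDs, correlations and arm splits. They also assume drop-out unrelated to score, so they do not represent exits prompted by starting an antidepressant, which are probably related to outcome. If LOCF was not intended, the sentence has no clear meaning and still needs rewriting.

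**What to change.** Rewrite the missing-data sentence in section 3.4 so that LOCF is no longer the primary rule. Analyse all observed MADRS visits with a likelihood-based mixed model containing arm, visit, arm × visit, baseline MADRS and the randomisation stratum (under 3 weeks v 3 weeks or more postpartum). Report the arm contrast at the time point that the sponsor designates as primary; the article designates none, and section 2.1 and Table 1 list different assessment times. Add one missing-not-at-random sensitivity analysis that covers participants who leave on starting antidepressants.

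The mixed model is valid if missingness depends only on observed data. It was not itself simulated here, and the sensitivity analysis is there for departures from that assumption.

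Sample size, visits and data collection do not change. The cost is analysis wording and one extra sensitivity analysis.

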## Abstract

Postpartum depression (PPD) is a complex combination of physiological, emotional, and behavioral alterations associated with postpartum chemical, social, and psychological variations. It does harm to the relationship between family members that could potentially last for years. However, standard depression treatments are not ideal for PPD, and the outcomes of these treatments are debatable. Transcranial direct current stimulation (tDCS) is an emerging technology that could provide patients with PPD with a safe and non-pharmacological treatment. tDCS can relieve depression by directly stimulating the prefrontal cortex through the excitatory effect of the anode. It may also ease depression indirectly by promoting the production and release of the neurotransmitter GABA. The mechanism of tDCS makes it an ideal therapeutic approach to treat PPD, although it has not been widely used, and its effect has not been evaluated systematically and effectively. A double-blind, randomized controlled trial will be conducted involving 240 tDCS-naive patients with PPD, who will be randomly divided into two groups. One group will receive routine clinical treatment and care with active tDCS, and the other group will receive routine clinical treatment and care with sham tDCS. Each group of patients will receive a 3-week intervention during which they will receive 20 min of active or sham tDCS 6 days per week. The Montgomery–Åsberg Depression Rating Scale will be administered before the intervention as a baseline and on each weekend throughout the intervention phase. Before and after the intervention, the Perceived Stress Scale and the Positive and Negative Affect Schedule will be evaluated. Side effects and abnormal reactions will be recorded during each treatment. As antidepressants are banned in the study, the results will not be affected by drugs and will therefore be more accurate. Nonetheless, this experiment will be conducted in a single center as a small sample experiment. Therefore, future studies are required to confirm the effectiveness of tDCS in treating PPD.

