Non-invasive brain stimulation (NIBS) is a non-traumatic, convenient, safe, and effective brain function therapy technique widely used in clinics. As a typical NIBS approach, transcranial direct current stimulation (tDCS) may be an effective brain stimulation medical technique with the potential to be an “optimal” treatment method for PPD. Additionally, tDCS, a local brain stimulation-based treatment approach, is dependent on the presence of abnormalities in the activity of the frontal lobe region of the brain, particularly the left and right dorsolateral prefrontal cortex (PFC) (George et al., 1997; Speer et al., 2000; Fitzgerald et al., 2003; Ardolino et al., 2005). In a meta-analysis of 10 studies, researchers found that, compared to sham tDCS, active tDCS was more favorable in alleviating symptoms of depression after 2 to 3 weeks of treatment (Kalu et al., 2012). Significantly, tDCS has proven to be safe in a wide range of trials. In one study involving the side effects of tDCS, 77 healthy controls and 25 patients with neurological diseases were examined 567 times, with the most prevalent side effects involving slight tingling, moderate fatigue, and mild tickling under the stimulation electrodes. After tDCS, approximately 10% of headaches and <3% of instances of insomnia and nausea were reported (Poreisz et al., 2007). Additionally, tDCS is an available treatment approach. The instrumentation required is cheap and mobile, and tDCS can be administered by trained technicians or by the individual themselves.

In summary, tDCS is a novel, safe, and non-pharmacological treatment technique for individuals suffering from PPD. The purpose of this protocol is to evaluate the efficacy and safety of tDCS as a method of treating PPD with a forward-looking, double-armed, sham-control, randomized controlled trial (RCT) protocol toP. This may be a guide to a larger multi-centered RCT that explicitly values the therapeutic effects of tDCS on the treatment of PPD. This study protocol may also be used to derive the initial impact dimensions for the sample size required to complete the most complete and reliable RCT.

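### The only between-group analysis named for side effects is a chi-square or Fisher test, which says little about excess harm for uncommon side effects; a risk difference with a confidence interval would

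*Protocol article*

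**What the plan says.** Section 1 (Introduction) puts safety beside efficacy: "The purpose of this protocol is to evaluate the efficacy and safety of tDCS as a method of treating PPD". The same section gives side-effect frequencies from an earlier study of 77 healthy controls and 25 patients with neurological disease: "After tDCS, approximately 10% of headaches and <3% of instances of insomnia and nausea were reported". It names tingling, fatigue and tickling as the most common effects but gives no rates for them, and it gives no sham rate for any effect.

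Section 3.4 (Statistical methods) names one between-group method for side effects: "The side effects will be displayed and parsed using a χ^2^ test or Fisher's precision test". It also says that discrete measures will be shown as percentages, so percentages per arm can be expected. It names no estimate of the difference between arms and no confidence limit for side effects.

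Section 2.5 (Sample size) bases the number of patients on improvement, with a 5% type I error and 90% power: "the estimated sample size requires 79 participants per group". After dropout, "at least 198 participants will be required to achieve the target of 79 participants in each group". The Abstract plans for "240 tDCS-naive patients with PPD, who will be randomly divided into two groups".

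Elsewhere the article provides for termination of the intervention (section 2.12), vital signs at each session and weekly monitoring of adverse outcomes (section 3), and daily safety evaluation with reporting to the ethics committees (section 3.5).

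**The concern.** For a safety purpose, the useful question is how large an excess of harm over sham the data still allow. A test of no difference does not answer it. With uncommon events and a sample chosen for efficacy, a p-value above 0.05 is the likely result whether or not active tDCS doubles the side effect, so it hardly separates the two cases.

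The article presents this trial as a pilot to guide a larger multi-centre study of efficacy and safety (section 4). The designers of that study will need the plausible range of excess risk. Two percentages and a p-value do not state that range.

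**Working it through.** **Inputs.** Type I error 5% (section 2.5; two-sided assumed, as the article does not say). Group sizes: 79 (section 2.5), 99 (198/2) and 120 (240/2, assuming equal allocation). Event rates: about 10% headache, under 3% insomnia and nausea (section 1). These are rates after tDCS, with no sham rate and no clear denominator, so every sham rate below is an assumption.

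**The plan's own figure.** At the upper dropout figure of 20%, 79/0.80 = 98.75, so 99 per group and 198 in total, as stated. The 79 cannot be re-derived because the two assumed proportions are not given. The printed formula, two-sided, gives 79 for 25% v 50%, for example: 2 × 0.375 × 0.625 × (1.960 + 1.282)² / 0.25² = 78.8. The article states no power or sample size for side effects.

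**Power of the named tests.** Exact power is the sum, over all pairs of event counts (x, y), of Bin(x; n, p0) × Bin(y; n, p1) for the tables that the test rejects at 0.05. The chi-square is uncorrected and the Fisher test two-sided. The miss rate is 1 − power.

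| Sham v active (assumed) | Missed at 79 per group: chi-square / Fisher | Missed at 120 per group: chi-square / Fisher |
|---|---|---|
| 3% v 6% | 86% / 94% | 81% / 89% |
| 5% v 10% | 77% / 86% | 68% / 78% |
| 3% v 9% | 63% / 77% | 48% / 61% |
| 10% v 20% | 57% / 66% | 41% / 48% |
| 20% v 40% | 21% / 26% | 7% / 9% |
| 10% v 30% | 10% / 14% | 2% / 3% |

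At 99 per group the results lie between; for 3% v 6% the miss rate is 85% / 91%.

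**Hand check by normal approximation.** Power = Φ{[d√n − 1.96√(2p̄q̄)] / √(p0q0 + p1q1)}, where d = p1 − p0. For 3% v 6% at 120 per group: (0.3286 − 0.5746)/0.2924 = −0.84, so power is 20%. At 79 per group: (0.2667 − 0.5746)/0.2924 = −1.05, so power is 15%. The exact chi-square values are 19% and 14%.

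**Where a doubling is missed more often than not.** Solving for 50% power gives a sham rate of about 12% at 79 per group, 9.9% at 99 and 8.4% at 120 (normal approximation; the exact chi-square agrees). Fisher's test is more conservative, with thresholds about 1.5 to 2 points higher.

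**What an interval would show.**
- 8/79 sham v 16/79 active gives Fisher p = 0.12. The Newcombe 95% interval for the excess is −1 to +21 percentage points.
- Equal observed rates of 3% give an upper 95% limit for the excess of 1.96√(2 × 0.03 × 0.97/n), which is +5.3 points at 79 per group and +4.3 at 120. At equal rates of 10% it is +9.4 and +7.6 points.
- No events among n active patients gives a one-sided 95% upper limit of 1 − 0.05^(1/n), which is 3.7% at 79 and 2.5% at 120.

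**The case against.** The case against has several parts.

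- **No rule equates non-significance with safety.** A reader might infer that p > 0.05 will be read as safe. The article contains no such rule, and its description of tDCS as safe in section 1 rests on earlier trials. This stands.
- **Safety is not judged by this test alone.** A reader might infer so, but sections 2.12, 3 and 3.5 provide termination criteria, monitoring and reporting, and percentages per arm are planned. This stands. Those provisions protect individual patients, however, and do not estimate excess risk against sham. A crude difference can be had by subtracting the percentages, but not its uncertainty.
- **A doubling would not usually be missed at every base rate.** At 120 per group, 10% v 20% is detected in 59% (chi-square) or 52% (Fisher) of trials. A tripling from 10% to 30% is detected in at least 86% at either size. Side effects are recorded at each session, so patients who later drop out still contribute, and 79 is a pessimistic denominator. This stands and limits the point to uncommon events.
- **The cited rates are weak inputs.** They come from 102 people examined 567 times, without a sham rate, and may not be per-participant rates. The error could run either way, which is why two assumptions are carried through.
- **This is a condensed article of a pilot, and a fuller document may add intervals.** That is possible, and the absence of a margin or a safety sample size is not held against the plan. But the article does choose a comparative method, and that method does not suit the stated purpose. Pilot status favours intervals, since they are what the next trial needs.

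**Conclusion.** The point holds for uncommon side effects. The named test is a poor basis for a comparative safety conclusion when the sham rate is below about 12% (79 per group) or 8% (120 per group), because a doubling would then be missed more often than not by chi-square. At the rates the article quantifies, a doubling is missed in 81% to 94% of trials for 3% v 6%, and in 68% to 86% for 5% v 10%, across both group sizes and both tests.

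These figures assume a two-sided 5% level, equal allocation, one count per participant and the stated sham rates. They do not show that the test is uninformative for common side effects or large excesses, or that the trial intends to declare safety from a non-significant result. This is an inexpensive improvement to the analysis, not an error that undermines the trial.

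**What to change.** In section 3.4, supplement the test as follows:

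- Count each participant once for each side effect.
- Report the number and percentage per arm, and the active-minus-sham risk difference with a 95% confidence interval (for example Newcombe or Miettinen-Nurminen).
- For side effects with zero or few cases, give an exact upper confidence limit.
- Keep the chi-square or Fisher p-values as descriptive.
- State that the safety conclusion will be worded from the upper limit, that is, the largest excess not ruled out, and that a non-significant test will not be taken as evidence of safety.

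The cost is one or two sentences and an extra table column, from data already collected. No non-inferiority margin and no additional patients are needed. The downside is a more cautious statement: which excess has been ruled out, in place of a finding of no significant difference.
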